## Abstract

**Background:**

Standard coronary artery bypass graft surgery uses a single internal mammary artery and supplemental vein or radial artery grafts. Several observational studies have suggested a survival benefit with two internal mammary artery grafts compared to a single internal mammary artery graft, but this has not been tested in a randomised trial. The Arterial Revascularisation Trial is a Medical Research Council and British Heart Foundation funded, multi-centre international trial comparing single internal mammary artery grafting versus bilateral internal mammary artery grafting.

**Methods/Design:**

Twenty centres in the UK, Australia, Poland and Brazil are planning to randomise 3000 coronary artery bypass graft surgery patients to single or bilateral internal mammary artery grafting. Supplemental grafts may be either saphenous vein or radial artery. Coronary artery bypass grafting can be performed as an on-pump or off-pump procedure. The primary outcome is survival at 10 years and secondary end-points include clinical events, quality of life and cost effectiveness. The effect of age, left ventricular function, diabetes, number of grafts, vein grafts and off-pump surgery are pre-specified subgroups.

**Discussion:**

The Arterial Revascularisation Trial is one of the first randomised trials to evaluate the effects on survival and other clinical outcomes of single internal mammary artery grafting versus bilateral internal mammary artery grafting, and will help to establish the best approach for patients requiring coronary artery bypass graft surgery.

## Background

Coronary artery bypass graft (CABG) surgery is the optimal therapy, prognostically and symptomatically, for multi-vessel ischaemic heart disease [1]. Worldwide, around 800,000 CABG are performed annually. Recognising the under provision of CABG in the UK, the National Service Framework (NSF) aims to increase numbers from 500 [2] to 750 per million of population. The requirement for CABG is also likely to increase because of a growing elderly population with coronary disease and because percutaneous interventions ultimately lead to an increased requirement for CABG [3].

Most CABG patients require three grafts and the standard operation uses a single internal mammary artery (SIMA) and supplemental vein or radial artery grafts (Figure 1). CABG provides excellent short and intermediate term outcomes but its long-term efficacy is limited by vein graft failure. Ten years after CABG around 1/2 of vein grafts are blocked and of the remaining 50% half are severely diseased [6] whereas up to 95% of internal mammary artery (IMA) conduits remain disease free. In addition to reducing long-term survival, vein graft failure significantly increases the risk of recurrent angina, late myocardial infarction and the need for further intervention [4-7]. Indeed, by 10 years after CABG >50% of patients have recurrent angina and up to 1/3 may eventually require redo CABG [8-11]. Aspirin and statins [10,11] may improve vein graft patency but are unlikely to achieve the patency rates of IMA grafts.

**Figure 1 F1:**
[figure not shown]
Schematic drawing showing typical examples of: (1) Single internal mammary artery (SIMA) grafts and (2–4) Bilateral internal mammary artery (BIMA) grafts. Key: IMA = internal mammary artery; RA = radial artery; SVG = saphenous vein graft.

As discussed below, bilateral IMA (BIMA) in comparison to SIMA grafts, may improve survival and reduce the need for redo CABG. However while BIMA grafting is common in some centres in Europe, America, Australia and Japan, it still not widely used. For example, in 1998 15% of UK CABG patients received two arterial grafts (and a significant proportion of these would have used a radial artery rather than a second IMA graft) [2]. The major reasons for not using BIMA grafts is because of no definitive evidence of benefits (there are no randomised trials) and the perceptions that it is technically more challenging, more prolonged and increases the risk of impaired wound healing. Given the number of CABG procedures currently performed in the UK and the aim of the NSF to increase these numbers, it is also important to obtain accurate information on the costs and cost-effectiveness of using BIMA versus SIMA grafts.

Nine studies, reviewed extensively in reference 12, have compared the influence of SIMA and BIMA grafts on survival and the need for redo surgery. Interpretation of individual studies is, however, complicated by lack of randomisation, small patient numbers and inadequate length or completeness of follow-up. Furthermore, as the use of BIMA grafts was initially confined to younger, lower risk patients, any long-term benefits were attributed to the inherently more favourable characteristics of these patients, obscuring any benefit of BIMA.

A recent systematic review was performed of those studies, meeting pre-specified criteria relating to patient selection, comparability of groups, outcome assessment, and completeness of follow-up, to determine if there are differences in survival, expressed as a pooled hazard ratio (HR), in patients receiving SIMA or BIMA [12] (Figure 2). The analysis included 15962 patients comprising 11269 SIMA and 4693 BIMA patients from seven studies that either matched or adjusted for age, sex, ventricular function and diabetes. The results suggested a survival advantage for BIMA grafts (HR for death = 0.81, 95%CI: 0.70 to 0.94) without any evidence of a detrimental effect, however there was very limited evidence relating to secondary endpoints including possible adverse consequences.

**Figure 2 F2:**
[figure not shown]
Survival following bilateral internal mammary artery (IMA) grafting compared to single IMA grafting [12].

In the largest single study [13], of 8000 SIMA and 2000 BIMA patients, Lytle *et al *reported that the HR for death was decreased by 23% in the BIMA group at 12 years and the need for redo CABG reduced from 40% in the SIMA to 10% in the BIMA group.

In another observational study, published after the systematic review, Endo *et al *reported outcome in 688 SIMA and 443 BIMA patients [14]. The groups were similar regarding age and ventricular function but there were more diabetics in the BIMA group (18% vs 13%) and females in the SIMA group (19% vs 10%). At six years the combined incidence of death, myocardial infarction and redo CABG was lower in the BIMA group (p = 0.06) and particularly in the 782 patients below 71 years and with an ejection fraction > 0.4 (HR: 0.61; 95%CI, 0.38 to 0.98:p = 0.04). As vein graft failure increases markedly beyond seven years after CABG the authors suggest that the benefits of BIMA grafts are likely to increase with further follow-up.

Two studies reported no benefit of BIMA grafting [15,16]. Sergeant's study, however, had fewer than 100 BIMA patients with 10-year follow up and use of the second IMA was frequently suboptimal [15]. Kurlansky et al reported no survival difference at ten years in 261 women with BIMA grafts and a matched cohort with SIMA grafts [16]. However, 81% of the BIMA group vs 66% of the SIMA group had triple vessel disease (p < 0.001) and only 120 patients in each group were available for comparison at ten years.

For optimal patency both IMA should be placed to the left sided arteries [17-19] (Figure 1). Patency of the right IMA is reduced if used as a free aortic graft [18] or placed to the right coronary artery [19] due to size discrepancy and eventual disease development at the crux.

Angiographic studies demonstrate markedly superior patency of BIMA grafts, compared to vein grafts, refuting the assertion that the superior patency of IMA grafts is due to better 'run-off' in the LAD territory. Patency rates for BIMA to various coronary arteries, are 98% at 7 days [14] and 95% at two [20] and seven years [21]. Furthermore, off-pump CABG (OPCAB) now makes CABG feasible in patients whose advanced age previously precluded CABG using cardiopulmonary bypass. A composite radial artery from one or both IMA, allows up to four grafts as an 'off-pump' CABG, eliminating both cardiopulmonary bypass and aortic manipulation and minimizing the risk of cerebral injury [22].

Opposition to BIMA grafting is largely based on the perception of increased perioperative risk and especially sternal wound morbidity. There is consistent evidence, however, that the operative mortality of BIMA grafting at 1%–2% [12,13] is no higher, and may, in fact, be less than that of the standard operation because of a reduced risk of early graft failure.

Sternal dehiscence is a potential complication of BIMA grafts and particularly in diabetics. In reality, there is only a minimal increase in the risk of impaired wound healing in both non-diabetics [13,23-27] and diabetics [23-27] unless the patient is morbidly obese and/or has marked respiratory impairment [24]. The risk of impaired wound healing can be minimized with judicious patient selection and modification of the IMA harvesting method whereby a 'skeletonized' rather than 'pedicled' fashion preserves collaterals and sternal blood supply [25] and improves wound healing, particularly in diabetics. No difference has been found in myocardial enzymes [28], parameters of respiratory exchange [29] or in respiratory injury between SIMA and BIMA patients. BIMA harvesting adds around 30 minutes to a three-hour operation.

Uncertainty remains because there is no randomised evidence, therefore a randomised trial – the Arterial Revascularisation Trial (ART) – has been designed to compare SIMA versus BIMA grafting in coronary revascularisation. ART will compare survival rates, need for redo CABG, other clinical events, quality of life and cost effectiveness of SIMA versus BIMA grafting.

The main objective of ART is to assess whether the use of both IMA during CABG (BIMA) improves survival and reduces the need for further interventions over that observed with a single IMA (SIMA).

## Methods/Design

### Trial design

Two-arm, randomised multi-centre trial. Patients will be randomised to SIMA or BIMA with supplemental vein or radial artery grafts as required.

### Eligibility

#### Inclusion criteria

• CABG patients with multi-vessel coronary artery disease (including urgent and off pump CABG patients)

#### Exclusion criteria

• Single graft

• Redo CABG

• Evolving myocardial infarction

• Concomitant valve surgery

### Randomisation and enrolment process

All patients requiring CABG should be considered for entry into the study. Centres should keep a screening log and record if the patient is entered into the study and if not the reason why not. Patients who meet the eligibility criteria and give written informed consent should be randomised.

Randomisation will be performed by telephone contact with the trial co-ordinating centre (the Clinical Trials and Evaluation Unit (CTEU) based at the Royal Brompton Hospital in London). The randomisation service will be available 09:00–17:00 (UK time). Centres will be asked for a few simple details about the patient including initials, date of birth and eligibility criteria. The caller will be given the procedure allocation (SIMA or BIMA) and a fax will be sent to the centre confirming this.

Eligible patients will be randomised in equal proportions between the two surgical strategies SIMA or BIMA. The allocated procedure will be performed by a trial nominated surgeon who has been approved by the Trial Steering Committee as being sufficiently experienced (ie. performed >50 BIMA procedures).

Randomisation will be stratified by centre with specific tables using block allocation to provide treatment distribution in equal proportions. The block size will itself be subject to random variation.

To reduce the possibility of outcome measure events occurring after randomisation and before revascularisation, surgery should be performed within 6 weeks of randomisation.

### Surgical procedure

It is left to the individual centres to decide the optimal anaesthetic technique and method of myocardial protection for each patient. As there is a consistent mortality of around 2.5% for CABG across most UK centres this suggests that minor differences in anaesthetic technique and methods of myocardial protection do not have a major influence on perioperative mortality. Surgical details will be recorded in the case report form (CRF). The only requirement is that the surgeon follows the randomisation allocation given for the patient (ie. SIMA or BIMA).

Surgery can be performed with cardiopulmonary bypass or as an off-pump procedure according to the experience of the surgeon.

The following surgical procedures should be applied depending on the allocation to SIMA or BIMA:-

**SIMA **– standard operation using SIMA to LAD plus supplemental vein or radial artery graft

**BIMA **– both IMA placed to left sided coronary arteries with supplemental vein or radial artery. The IMA grafts can be used as composite grafts to each other, as long as one remains *in situ*.

Possible combinations include

• LIMA to OM and RIMA to LAD

• LIMA to LAD and RIMA to OM (via transverse sinus)

• LIMA to LAD and RIMA as composite graft to OM

Some typical examples of SIMA and BIMA grafts are shown in Figure 1.

Please note that anastomosis of an IMA graft to the right coronary artery is an exclusion criteria (because of evidence of inferior long-term patency).

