### Trial size

#### Number of patients

To achieve an absolute 5% reduction in 10-year mortality (ie from 25% to 20%), with 90% power at 5% alpha requires 2928 patients. The mortality data is taken from a summary of previous studies published in reference 12.

The aim is to enrol at least 3000 patients (1500 in each arm) over a 2 to 3 year recruitment period in 20 centres in the UK, Australia, Poland and Brazil (Table 3). As the intervention is the operation, compliance is likely to be 100% except in the unusual situation where the planned operation is not possible for technical reasons.

**Table 3 T3:** ART Principal Investigators and centres

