### Statistical issues

#### Type of analyses

The trial data will be analysed on an intention-to-treat basis with patients included in the groups assigned at randomisation, irrespective of future management and events. Outcome measure event tracking will begin at randomisation and continue until death or the end of follow-up. Analysis of time to event data will use log rank tests and possibly other methods suitable for survival data, in particular to take account of known prognostic variables.

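### The right-coronary exclusion is missing from the eligibility list and is worded as a graft placement, so the printed criteria admit some patients who cannot receive BIMA as defined

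*Protocol article*

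**What the plan says.** All references are to the protocol article.

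- **Inclusion and Exclusion criteria.** CABG patients with multi-vessel disease are eligible. Four exclusions are listed: single graft, redo CABG, evolving myocardial infarction and concomitant valve surgery. None concerns the right coronary artery or the number of left-sided targets.
- **Randomisation and enrolment process.** "Patients who meet the eligibility criteria and give written informed consent should be randomised". On the telephone call, "Centres will be asked for a few simple details about the patient including initials, date of birth and eligibility criteria".
- **Surgical procedure.** BIMA means "both IMA placed to left sided coronary arteries with supplemental vein or radial artery"; SIMA means a single IMA to the LAD plus vein or radial grafts. The section ends by noting that "anastomosis of an IMA graft to the right coronary artery is an exclusion criteria", giving inferior long-term patency as the reason.
- **Number of patients.** 2928 patients are needed to detect a fall in 10-year mortality from 25% to 20% with 90% power at 5% alpha; the target is at least 3000 (1500 per arm). The section expects that "compliance is likely to be 100% except in the unusual situation where the planned operation is not possible for technical reasons".
- **Type of analyses.** Intention to treat, with "patients included in the groups assigned at randomisation, irrespective of future management and events".

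**The concern.** The article prints a list of exclusions and later names one more that is not on it. A centre working from the eligibility sections alone would not apply the extra item. A centre that does apply it must decide what it means: that patients for whom such a graft is planned should not be entered, or that surgeons must not make that anastomosis.

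Neither reading asks whether the patient has two left-sided arteries suitable for IMA grafts, which is what decides if BIMA as defined can be done. Consider a patient with disease of the LAD and the right coronary artery and no other graftable left-sided branch. This is multi-vessel disease needing more than one graft, so the patient passes the printed criteria. Allocated SIMA, the patient can have the defined operation. Allocated BIMA, the patient cannot. The surgeon would have to give SIMA, place an IMA to the right coronary artery against the rule, or depart from the definition in some other way.

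Under intention to treat such patients stay in the BIMA arm and pull its mortality towards that of SIMA. In a trial with a 10-year primary endpoint, that dilution cannot be undone after recruitment closes.

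**Working it through.** **1. The affected group.** Needing a right-coronary graft does not by itself rule out BIMA, because the definition allows a supplemental vein or radial graft, which can go there. The three combinations shown are labelled as possible ones, so left-sided branches other than the obtuse marginal count as targets. Composite IMA grafts are allowed if one IMA stays in situ. The group is therefore only those multi-vessel patients with no second left-sided target of any kind. The article does not say how many there are.

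**2. The plan's own sample size.** Inputs from Number of patients: p1 = 0.25, p2 = 0.20, power 90%, alpha 5%. Sidedness is not stated; two-sided reproduces the figure, while one-sided gives 2386. With pooled variance, no continuity correction and p̄ = 0.225:

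n per arm = [1.960·√(2p̄(1−p̄)) + 1.2816·√(p1(1−p1) + p2(1−p2))]² / (p1−p2)²

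= [1.960 × 0.5906 + 1.2816 × 0.5895]² / 0.05²

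= (1.1575 + 0.7555)² / 0.0025 = 1463.7, rounded up to 1464, or 2928 in total.

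This matches exactly with zero crossover and zero dropout. The target of 3000 adds 72 patients (2.5%).

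**3. Illustrative dilution.** Let f be the share of randomised patients who cannot have BIMA as defined and receive SIMA if allocated BIMA. The article gives no value, so f is an assumption. Assume also that these patients have the same 25% mortality on SIMA as everyone else. BIMA-arm mortality becomes p2 = 0.20 + 0.05f, and with n = 1500 per arm:

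power = Φ{[(p1−p2)·√n − 1.960·√(2p̄(1−p̄))] / √(p1(1−p1) + p2(1−p2))}

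For f = 5%: p2 = 0.2025 and p̄ = 0.22625, giving (1.8397 − 1.1597) / 0.5908 = 1.151, so power is 87.5%.

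| Assumed f | Power if randomised (1500 per arm) | Power if screened out, not replaced | n per arm if not replaced |
|---|---|---|---|
| 0% | 90.7% | 90.7% | 1500 |
| 2% | 89.5% | 90.1% | 1470 |
| 5% | 87.5% | 89.2% | 1425 |
| 10% | 83.7% | 87.6% | 1350 |

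Power reaches 90% at f = 1.17%, or about 1.2%. If the screened-out patients are replaced, power is 90.7% in every row. Under these assumptions, screening them out costs less power than randomising them, even without replacement. The higher rows only show the shape of the curve; nothing in the article suggests this anatomical group is that large.

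**The case against.** The case against is substantial, and much of it stands.

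- **The sentence can be read as a screen on the planned operation.** Three of the four listed exclusions (single graft, redo CABG, concomitant valve surgery) are also operation terms, and they are plainly applied before randomisation. This stands: the wording is ambiguous, and it would go too far to say it cannot be applied before allocation. Even on this reading, though, it does not ask about two left-sided targets.
- **A reader might infer that surgeons are told to deliver an impossible operation,** because the section says "The only requirement is that the surgeon follows the randomisation allocation given for the patient". The text does not support that. The sentence closes a paragraph leaving anaesthetic technique and myocardial protection to centres, and the sample-size section recognises that an operation may prove technically impossible.
- **A reader might infer that patients would be removed after randomisation, almost only from the BIMA arm.** Nothing in the article says so, and the intention-to-treat statement points the other way.
- **Non-compliance is already addressed.** The article calls technical failure unusual, restricts operators to approved surgeons with more than 50 BIMA procedures, and aims for slightly more than 2928. This stands as a judgement the article gives no data to overturn. The Background also says that most CABG patients need three grafts, which suggests the affected group may be small.
- **An IMA placed to the right coronary artery is a deviation, not necessarily a crossover to SIMA.** This stands; the table assumes full loss of benefit.
- **The article is condensed, and sites also have a full protocol, a Manual of Operations and training.** Finer anatomical guidance may be there. The point here is narrower: the article prints an exclusion outside its own eligibility list, in a form open to two readings.

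**Conclusion.** The point holds as a defect of placement and wording that affects who is randomised. The right-coronary item is called an exclusion criterion but is absent from the list, and the printed criteria admit patients without two left-sided targets. Such patients cannot receive BIMA as defined and, if allocated to it, would probably cross over or deviate.

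The effect on the trial is dilution of the intention-to-treat difference by an unknown and possibly small amount. The figures of 89.5% power at 2% and 87.5% at 5% are illustrations. They rest on an assumed rate, full crossover to SIMA with no benefit, and equal underlying mortality. A reader might conclude that the stated 90% power is wrong. That is not shown: 2928 is correct on its own terms, and 3000 patients tolerate about 1.2% crossover. Severity is minor to moderate, and the case for acting rests mainly on how little the change costs.

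**What to change.** 1. **Eligibility (Inclusion and Exclusion criteria).** Add: before allocation is disclosed, the trial surgeon judges that both SIMA and BIMA, as defined under Surgical procedure, are feasible, with at least two left-sided targets suitable for IMA grafts. Confirm this on the randomisation call, which already asks about eligibility.
2. **Surgical procedure.** Replace the right-coronary sentence with a surgical rule, for example: an IMA must not be anastomosed to the right coronary artery.
3. **Number of patients (optional).** State that 2928 assumes no crossover and that 3000 keeps 90% power up to about 1.2% BIMA-to-SIMA crossover, with illustrative values beyond that.

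The cost is one eligibility line, one reworded sentence, one question on a call already made and, optionally, one sentence on power. No extra tests, staff or patients are required by design. The downsides are a slightly narrower population, by an amount the article does not allow one to estimate, and some surgeon judgement at entry. Switches decided during surgery would remain.

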### Outcome measures

#### Primary

• Death from any cause (cardiovascular and non-cardiovascular mortality).

*This outcome will be recorded using the flagging system of the Office of National Statistics (using name, address, date of birth and NHS number)*.

